## Abstract

**Significance:**

Due to caregiving commitments, caregivers of older adults may not have the time to make use of the onsite community services available to them during the day. With the support of advanced technology, telecare could be a convenient and easily accessible channel for providing individualized caregiving advice to caregivers.

**Objective:**

The aim of the study is to describe a research protocol that highlights the development of a telecare-based intervention program for reducing stress levels in informal caregivers of community-dwelling older adults.

**Methods:**

It is a randomized controlled trial. The study is supported by two community centers. The study participants will be randomly assigned to either the telecare-based intervention group or the control group. The former will receive a 3-month program comprised of three components: online nurse case management supported by a health and social care team, an online resource center, and a discussion forum. The latter will receive the usual services that provided by the community centers. Data will be collected at two time points – pre-intervention (T1) and post-intervention (T2). The primary outcome is stress levels, while secondary outcomes include self-efficacy, depression levels, quality of life, and caregiving burden.

**Discussion:**

Besides taking care of one or more older adults, informal caregivers have to deal with work, chores, and take care of their children. This study will add valuable information to the knowledge gap on whether telecare-based interventions with the support of an integrated health-social team can alleviate the stress levels of informal caregivers of community-dwelling older adults. If successful, policymakers and healthcare professionals should consider incorporating telecare modalities in a primary health setting for informal caregivers to correspond with them, to relieve their caregiving stress and promote a healthy life.

**Clinical trial registration:**

https://www.clinicaltrials.gov/, NCT05636982.

## Introduction

Aging populations have become a global trend. By 2050, there will be nearly 2.1 billion people over the age of 60 – double the figure in 2017 (1). The continuously growing number of older adults will inevitably lead to a greater demand for home-based care and health-related services. In Asian countries and regions like Hong Kong, many older adults are receiving daily care from family members (i.e., 37.3% from their adult children and 26.3% from their spouse) (2). Despite their lack of caregiving skills and knowledge, research has shown that informal caregivers play a better caregiving role than do paid healthcare providers due to their strong affiliation with their older family members (3). A recent study showed a more than 20% reduction in hospital readmission rates for older adults when informal caregivers were involved during the process of planning their discharge care (4). A business survey from the United States estimated that the economic value of family caregiving for their unpaid contributions was approximately $470 billion in 2017, which greatly exceeds the value of paid home care (5). Despite these benefits to older adults, healthcare providers, and the society, the increasing reliance on informal caregivers to provide daily care to older adults may eventually place a great deal of burden and stress on the caregivers, leading to physical and emotional distress and great frustration.

An informal caregiver, which refers to an extended family member or friend who volunteers to take care of an older adult at home, usually handles different caregiving tasks in daily life, such as providing personal care, preparing meals, giving medications, and monitoring health conditions. In a qualitative study, the majority of caregivers reported while that caregiving is rewarding and their relationship with their older relative benefits from the caregiving experience, their busy caregiving role has jeopardized their personal life and commitments. For those with a full-time job and children to care for, the huge demand of providing caregiving duties to an older family member has been known to negatively affect their physical, social, financial, and emotional health. A recent survey reported that more than 60% of informal caregivers perceived that they had a heavy caregiving burden, 55% had depressive symptoms, 40% had poor family function, and 27% of them reported poor self-rated health (6). The emotional and physical demands involved in caregiving have a negative impact on the resilience of caregivers. That is why researchers and policy makers around the world have attempted to adopt different strategies to maintain and improve the health of informal caregivers and help them to perform caregiving roles.

Unlike the United Kingdom and the United States where there are structured health-social partnership frameworks, Hong Kong does not have an explicit cross-sectoral mechanism in place that facilitates information sharing among various health and social care sectors, resulting in the redundant and fragmented provision of services to both older adults and their informal caregivers (7, 8). It has been pointed out that there may be a range of different supporting services in the community available to caregivers, but they find it challenging to access the fragmented system to obtain the needed resources (9, 10).

With the rapid development of health information technology, people can now access health and social care services at home with ease. Telecare is defined as a remote intervention that allows healthcare professionals to assess the health status of clients, and provide education or deliver health and social care to them through information, communication, and monitoring technologies (11). Telecare is particularly useful to informal caregivers who find it challenging to meet healthcare professionals onsite and who have had difficulties in receiving caregiving advice due to full-time work commitments. Telecare not only allows informal caregivers to obtain caregiving information at their own time and pace, but also provides a virtual communication channel for informal caregivers and healthcare professionals from multiple disciplines to exchange caregiving ideas, seek health and social advice for their loved one, and receive physical and emotional support for their own health. Due to its many advantages, a US-based study found that more than 90% of informal caregivers were willing to participate in telecare programs that could facilitate their caregiving work and reduce their caregiving burden (12).

While studies have started to test the effectiveness of telecare on the health of older adults with multimorbidity (13), as well as on the health of young adults (14), to the best of our knowledge, the research has yet to extend to informal caregivers. Therefore, an attempt is made in this study to develop a telecare program, with the integrated efforts of a health-social team, to reduce the stress levels and caregiving burden, and improve the self-efficacy, depression levels, and quality of life of informal caregivers of community-dwelling older adults, and submit that program to empirical testing. If proven successful, policymakers and healthcare professionals should consider incorporating telecare modalities in primary health settings to correspond with informal caregivers to relieve their caregiving stress and promote a healthy life.

## Conceptual framework

Lazarus and Folkman’s Transactional Theory of Stress and Coping (TTSC) and the Creativity, Optimism, Planning and Expert Information (COPE) model will be used to guide the development of components of the intervention (15). The TTSC defines stress as resulting from an imbalance between environmental demands and individual resources. When applied to the informal caregivers of older adults, the environmental demands could include inadequate caregiving knowledge and skills, a lack of time to search for available supporting services, and inadequate physical and emotional care support; while individual resources may comprise education from healthcare professionals on caregiving knowledge and skills, community services for caregivers, and support from peers, friends, and family. To overcome the imbalance, the theory suggests two broad categories of coping mechanisms: problem-focused coping and emotion-focused coping. The aim of problem-focused coping is to manage the causes of the stressors, while emotion-focused coping is about managing the emotional distress caused by the stressors. Effective coping can lead to positive outcomes such as a reduction in the stress and depression levels of caregivers.

The COPE model will be used to guide the development of both problem-focused and emotion-focused coping strategies (16). *Creativity* refers to the adoption of innovative ways to increase the self-efficacy of an individual. *Optimism* encourages an individual to have positive thoughts about managing tasks perceived to be difficult. *Planning* is conducted with healthcare professionals after they assess and identify an individual’s specific problems and needs. *Expert Information* will be given to relieve the physical and emotional distress of an individual. Figures 1, 2 illustrate the framework.

**Figure 1 fig1:**
[figure not shown]
Lazarus and Folkman’s Transactional Theory of Stress and Coping.

**Figure 2 fig2:**
[figure not shown]
The COPE model.

## Methods

The SPIRIT statement was used as a guideline for this protocol paper (17).

### Aim

The aim of the study is to evaluate the effectiveness of a telecare-based intervention on stress levels in informal caregivers of older adults.

### Study design and setting

This is a single-blinded, two-armed, randomized controlled trial, where the research assistant who is responsible for data collection is blinded but the provider is not blinded. This study is supported by two community centers of a non-governmental organization.

### Participants and recruitment strategy and randomization

A trained community center staff member will help to generate a list of potential subjects from their membership list. Potential subjects will be called and recruited into the program if they fulfill the following inclusion criteria: (1) aged ≥18 years old, (2) have no cognitive impairment as evidenced by a score of 22 or above in the Hong Kong version of the Montreal Cognitive Assessment (18), (3) can understand and communicate in Cantonese, (4) provide care to older adults aged ≥60 at least 4 h per week for a minimum of 3 months, (5) use a smartphone, (6) know how to access the Internet, (7) commit to attending bi-weekly, 15–30 min online meetings with the program providers over the 3-month period, and (8) are willing to receive individual-specific video messages covering caregiving skills via WhatsApp. They will be excluded if they are (1) known to have serious alcohol and drug problems, (2) are unable to write and read, (3) have mental health problems, and (4) have already participated in other telecare health or social programs. When two or more potential subjects are taking care of the same older adult, only the one who has spent more time with the older adults is allowed to participate.

A trained research assistant (RA) will introduce the program and invite eligible subjects to join the program in the community centers, and obtain verbal consent upon their agreement. After collecting their baseline data, the research assistant will call the principal investigator (PI) of the research team for randomization. The PI will put the numbers generated from a software program called “Research Randomizer” into sealed envelopes (i.e., “1” = intervention group, “2” = control group). These envelopes will be opened sequentially when a call is received from the RA. In this study, the RA and the community center staff will be blinded, but the PI and the healthcare providers will not.

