### Control group

Both intervention and control group participants will receive services from the community centers as usual. The community centers will provide regular onsite educational sessions and workshops for enhancing the caregiving knowledge of caregivers. Attendance at these lectures is not mandatory, and all subjects are welcomed to join.

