## Data processing and analysis

The Statistical Package for the Social Sciences (SPSS) version 26.0 will be used to conduct a statistical analysis. The demographic data of the intervention and control groups will be compared at baseline, using appropriate tests (i.e., Mann–Whitney U, *t*-tests, or chi-square). Depending on the normality of the data, an independent *t*-test or a Mann–Whitney *U* test will be used to determine the group differences in both primary and secondary outcomes in T2. Intention-to-treat will be employed as the primary analysis in this study. Potential covariates, such as the duration of caregiving, the number of caregiving hours per week, and the number of referrals will be examined. Within-group differences will be analyzed using either the Wilcoxon signed-rank test (non-parametric) or a paired t-test (parametric). A significant result is indicated when the *p*-value (level of significance) is less than 0.05 for a two-tailed test.

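### Allocation as described makes no provision for the two centres or for blocking, and the T2 comparison has no centre term: a minor and cheaply repaired weakness that does not bias the result

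*Protocol article*

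**What the plan says.** All references are to the protocol article.

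- **Study design and setting:** "This study is supported by two community centers of a non-governmental organization".
- **Participants and recruitment strategy and randomization:** candidates come from the centres' membership list, compiled by centre staff. After baseline data collection the research assistant (RA) calls the principal investigator (PI). On the sequence, the text says "The PI will put the numbers generated from a software program called" Research Randomizer into sealed envelopes, coded 1 for intervention and 2 for control, and then "These envelopes will be opened sequentially when a call is received from the RA". Centre, strata, blocks and separate envelope sets are not mentioned.
- **Control group:** "Both intervention and control group participants will receive services from the community centers as usual". These services include onsite teaching: "The community centers will provide regular onsite educational sessions and workshops for enhancing the caregiving knowledge of caregivers". Uptake is voluntary: "Attendance at these lectures is not mandatory, and all subjects are welcomed to join".
- **Sample size:** 34 per group, raised for 15% drop-out to 40 per group, 80 in total.
- **Data processing and analysis:** an independent t-test or "Mann–Whitney *U* test will be used to determine the group differences in both primary and secondary outcomes in T2". On adjustment: "Potential covariates, such as the duration of caregiving, the number of caregiving hours per week, and the number of referrals will be examined". Centre is not among these examples, nor among the baseline variables under Background demographic data.

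**The concern.** Centre is the one structural grouping that the design itself creates. It fixes which membership list a caregiver comes from and which onsite sessions are on offer. A sequence that takes no account of centre can, by chance, put more of one centre's members in one arm, and an unadjusted two-group test leaves the resulting shift in the estimate. With 80 people such gaps are not negligible. If stress at T2 also differs between the centres, part of that difference enters the estimate in that trial, and a reader could not separate it out unless centre had been recorded and adjusted for.

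A second consequence follows from the same passage. The sample size relies on 40 per group, but no restriction on the sequence is described that would deliver it.

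**Working it through.** **Inputs from the article:** N = 80, 40 per group, two centres, planning effect 0.403, two-sided alpha 0.05. The 40 follows from the drop-out step: 34/0.85 = 40.

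**Assumed, because the article does not give them:** centre splits of 50:50, 70:30 and 80:20; a centre difference D of 0.2 or 0.5 SD in T2 stress; 0.403 read as a standardised mean difference; all 80 participants observed.

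**1. Size of a chance gap.** Let K participants come from centre A, and let X of them fall in the intervention arm. With 40:40 arms and no stratification, X is hypergeometric (80, K, 40). The gap in centre share is (2X − K)/40. Var(X) = 40 × p(1 − p) × 40/79 with p = K/80, and SD(gap) = 2·SD(X)/40. For K = 40, Var(X) = 40 × 0.25 × 40/79 = 5.06, SD(X) = 2.25, and SD(gap) = 0.1125.

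| Centre split | SD of gap (points) | P(gap ≥ 10) | P(gap ≥ 20) |
|---|---|---|---|
| 50:50 | 11.3 | 50.3% | 11.7% |
| 70:30 | 10.3 | 46.5% | 8.7% |
| 80:20 | 9.0 | 40.2% | 4.8% |

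For the 50:50 split, P(gap ≥ 15 points) is 26.3%.

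**2. Effect on the estimate.** Shift = gap × D. At a 20-point gap this is 0.20 × 0.2 = 0.04 SD or 0.20 × 0.5 = 0.10 SD, that is 10% or 25% of 0.403. At a 10-point gap it is 0.02 or 0.05 SD. For scale, the standard error with 40 per arm is √(2/40) = 0.224 SD, so even 0.10 SD is under half a standard error (0.10/0.224 = 0.45).

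**3. Long-run behaviour.** Simulation of 10,000 trials per scenario with a 50:50 centre split. *Present* means unstratified and unadjusted; *stratified* means balanced within centre with a centre term.

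| D | Type I error, present | Mean estimate, present (true 0.403) | Power, present | Power, stratified |
|---|---|---|---|---|
| 0.2 | 5.2% | 0.403 | 42.3% | 43.5% |
| 0.5 | 4.9% | 0.400 | 40.3% | 43.0% |

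The simulation error of each power figure is about √(0.43 × 0.57/10,000) = 0.5 points. A closed-form check agrees. Ignoring centre raises the outcome variance from 1 to 1 + D²/4, so the effect shrinks to 0.403/√1.01 = 0.401 or 0.403/√1.0625 = 0.391. With 40 per arm the t-test power is then 42.5% or 40.8%, against 42.9% with a centre term. The loss is 0.3 or 2.1 points by this route, and 1.2 or 2.7 points by simulation: roughly 0 to 3.

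Power is near 43% rather than 80% because 34 per group does not follow from 0.403 read as a standardised mean difference. That is a separate matter from centre. At an effect of 0.69, which 34 per group would detect with 80% power, the simulated loss is 86.4 − 86.1 = 0.3 points (D = 0.2) or 86.0 − 84.1 = 1.9 points (D = 0.5).

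**4. Stratifying without adjusting.** With D = 0.5 and balance within centre but no centre term, the simulated type I error falls to 4.0%. The test becomes conservative, so the centre term belongs with the stratification.

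**5. The 40:40 split.** If the generator is unrestricted (assumed), the arm size is Binomial(80, 0.5): P(exactly 40:40) = 8.9% and P(35:45 or worse) = 31.4%. At 35:45 the harmonic mean arm size is 2 × 35 × 45/80 = 39.4 against 40, a loss of about 1.6%. The smaller arm would keep 35 × 0.85 = 29.75, about 30 people, against the 34 stated as required.

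**The case against.** The strongest reply has four parts.

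- **The single sequence is inferred.** The article never says that one list serves both centres, and sequential opening would also fit one envelope set per centre. Articles often leave stratification and block details to the full protocol. This stands as a caution. The article does, however, set out the software, coding, envelopes and calls step by step, and an unstratified sequence is the natural reading of it.
- **Usual services are not peculiar to the control arm.** A reader might infer that the comparator itself varies by centre while the intervention does not. The Control group section does not support this: both arms receive the centres' services, and attendance is optional for all. Both centres belong to one organisation, and no difference in services or clientele is documented. This stands in full, and is why D is only an assumption.
- **Chance imbalance is not confounding.** A reader might infer that a centre difference is built into the treatment effect. It is not: the estimate is unbiased over randomisations, and the test's error rate already allows for chance imbalance. This also stands in full. What is left is a possible shift in one realised trial and a small loss of precision.
- **Nothing rules out adjustment.** The covariate list is open-ended, centre is known from the recruiting list, and pre-filled envelopes could hold exactly 40 of each code. All of this is possible, but none of it is written. The comparison that is named is unadjusted, and no restriction on the sequence is described.

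**Conclusion.** The point holds as a minor design weakness. As described, allocation takes no account of centre and names no blocking, and the T2 comparison has no centre term. The consequence is limited to precision and to bad luck in one trial: a centre gap of 20 points or more has about a 5% to 12% chance, with a shift of 0.04 to 0.10 SD when it occurs, and the power cost is roughly 0 to 3 points. Only gaps of about 10 points are close to an even chance, and those shift the estimate by at most 0.05 SD under the same assumptions.

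These figures rest on assumed centre splits and centre differences; the article gives neither. The doubt about 40:40 rests on the further assumption of an unrestricted generator. The documents do not support a claim of bias, of an inflated type I error, or of a comparator that differs between centres.

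**What to change.** State whether allocation is stratified by centre and whether it is blocked. If this is not yet fixed:

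1. Generate one sequence per centre in randomly permuted blocks, with block sizes unknown to the RA. The PI opens the next envelope from the set of the calling participant's centre. This also keeps the arms close to 40:40.
2. Record centre at T1.
3. Include centre as a fixed term in the between-group comparison at T2, for example in a linear model, since the t-test and the Mann–Whitney test as named carry no such term.

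If recruitment has begun, leave the sequence alone, record centre, and adjust for it.

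The cost is a second envelope set, slightly more bookkeeping, one indicator variable and one degree of freedom. No extra participants or visits are needed.

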### Interventions

This study is a 3-month program involving two parallel groups.

### Intervention group

Each intervention group subject will receive three intervention components: (1) online nurse case management supported by a health-social partnership team, (2) individual-specific video messages covering caregiving skills sent via WhatsApp, and (3) an online information center and discussion forum via a password-protected, newly-developed caregiver website.Online nurse case management supported by a health-social partnership team

Each intervention group subject will be assigned to a nurse case manager (NCM) during the first week of the program. The NCM has extensive experience in providing care to informal caregivers and has been trained specifically for this program. She will meet with the subjects bi-weekly via Zoom. The time of the meetings will be settled with the agreement of both the NCM and the subjects. In the first Zoom consultation, the NCM will assess the caregiving needs and problems of the subjects by using a structured and validated assessment-intervention-evaluation tool: The Omaha System. The Omaha System consists of 42 problems under four domains ─ environmental, psychological, physiological, and health-related behaviors (19). The NCM will empower the subjects to set goals and develop a personalized care plan tailored to their identified caregiving needs and problems. The goals and care plan will be followed up and revised in subsequent Zoom consultation sessions. The NCM will also provide emotional support, encourage the subjects to discuss their concerns, identify perceived challenges to achieving their goals, and together with the subjects find solutions in the Zoom consultation sessions on how to tackle these barriers. When deemed necessary, based on a jointly developed protocol and the problems of the subjects, the NCM will refer the subjects to one of the health-social partnership team members, which includes social workers, traditional Chinese medicine practitioners, a physiotherapist, and a mental health nurse. The protocol indicates the roles and responsibilities of each member in the health and social team, the suggested assessment, interventions and an evaluation scheme for each member, and the arrangement and logistics of the program. A monthly conference will also be held among the team members to review the referred subjects’ condition, care plans, and goal status.Individual-specific video messages covering caregiving skills sent via WhatsApp

In addition to online case management sessions, the NCM will send weekly, individual-specific videos of tips and reminders to the informal caregivers via WhatsApp, an interactive communication application. The subjects will receive videos that include, but are not limited to, the topics of common chronic diseases and their management, caregiving skills and techniques, available community services and resources, and self-care strategies. All of the videos originate from reliable organizations such as the Hospital Authority, Department of Health, and The Hong Kong Council of Social Service. To ensure the subject understands the content of the videos, the NCM will also teach and explain the content of the video, and answer any questions that they have during the online consultation sessions.Online information center and discussion forum accessed via a password-protected, newly-developed caregiver website

The research team will work with a technology company to design a website that incorporates two features, an online information center and a discussion forum. In the online information center, the members of the health-social team will regularly post general information to the informal caregivers that have been proven to be effective for them, such as family relationship management strategies, stress relieving techniques, and physical and mental health protection skills. In the discussion forum, the subjects can raise questions, either in the form of text, video, or both text and video to the health-social team members. To answer the questions, the team members will browse the discussion forum every 3 days at minimum. The forum can also serve as a peer-support platform where all of the caregivers in the intervention group can share their individual caring experiences, discuss commonly encountered issues, and seek emotional support from their peers. Peers with a similar background and experiences are believed to have a better understanding of their feelings and to be able to provide support to and receive consolation from each other. The website is only accessible to the health social team members and members of the intervention group, who will be given a preset password and username to log in. The subjects will also be told not to disclose the password to the others and all the information posted can be viewed by the people who is allowed to access the website.

